### Primary Efficacy Endpoints

For the change and percent change in HbA1c, descriptive statistics will be presented at baseline and at 24 weeks. The change from baseline to 24 weeks will be analyzed using mixed-effects models or generalized estimating equations (GEE) to account explicitly for clustering effects. Patient-level covariates identified as significantly imbalanced at baseline (SMD > 0.1) will be included as fixed effects, and inter-center variability as random effects.

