**Schedule for Data Collection in Clinical Study**

| **Collection  Schedule**  **Collection Items** | **Baseline** | **Follow-Up Visits  (Option, ☎)** | **Follow-Up Visits** | **Follow-Up Visits  (Option, ☎)** | **Close-Out Visit (COV)** |
| --- | --- | --- | --- | --- | --- |
|  | Visit 1 | Visit 2 | Visit 3 | Visit 4 | Visit 5 |
|  | 0 day | Week 6  (±2 Weeks) | Week 12 (±2 Weeks) | Week 18 (±2 Weeks) | Week 24 (±2 Weeks) |
| Obtain Written Consent^1)^ | ○ |  |  |  |  |
| Inclusion/Exclusion Criteria Confirmation | ○ |  |  |  |  |
| Assignment of Randomization Number | ○ |  |  |  |  |
| Installation of Well Check and Link to Institution | ○ |  |  |  |  |
| Demographic Information^2)^ | ○ |  |  |  |  |
| Information on Type 2 Diabetes^3)^ | ○ |  |  |  |  |
| Medical History Survey^4)^ | ○ |  |  |  |  |
| Alcohol/Smoking/Lifestyle Habits^5)^ | ○ | (○) | ○ | (○) | ○ |
| Physical Measurement^6^ | ○ | (○) | ○ | (○) | ○ |
| Vital Signs^7)^ | ○ | (○) | ○ | (○) | ○ |
| Body Composition Analysis (InBody) Test ^8)^ | (○) | (○) | (○) | (○) | (○) |
| Prior/Concomitant Medications^9)^ | ○ | (○) | ○ | (○) | ○ |
| Laboratory Tests^10)^ | ○ | (○) | ○ | (○) | ○ |
| Frequency of Well Check Use (Number of Login Days) |  |  |  |  | ○ |
| Well Check Usage Satisfaction Survey^11)^ |  |  |  |  | ○ |

*There are no additional visits or laboratory tests conducted specifically for this clinical study. In a routine clinical setting, it is recommended to collect data at 6-week intervals from Visit 1 (Baseline, Day 0) to 24 weeks (Visit 2: 6 weeks, Visit 3: 12 weeks, Visit 4: 18 weeks, Visit 5: 24 weeks). Visit 2 (6 weeks) and Visit 4 (18 weeks) can be optional visits and data can be collected via phone calls, based on the investigator (responsible physician )'s discretion. If a subject withdraws or drops out from the study, the data collected up to that point should be recorded in the case report form to the maximum extent possible.

1. Written consent must be obtained before performing any clinical study procedures. The date of written consent and Visit 1 (Baseline, Day 0) may differ, but consent must be obtained before participation in the clinical study.
2. Collect demographic information [initials, gender, age (month and year of birth), pregnancy and breastfeeding status].
3. Collect information on Type 2 Diabetes (date of diagnosis).
4. Collect medical history within 6 months prior to Visit 1 (Baseline, Day 0).

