# Evaluation Criteria and Methods, and Statistical Analysis Methods

## Endpoints

1. **Efficacy Endpoints**
2. **Primary Efficacy Endpoint**

- Percent change and change of HbA1c at 24 weeks compared to baseline

1. **Secondary Efficacy Endpoints**
   1. Percent change and change of FPG at 6, 12, 18, and 24 weeks compared to baseline
   2. Percent change and change in HbA1c at 6, 12, and 18 weeks compared to baseline
   3. Proportion of subjects achieving HbA1c < 7% at 6, 12, 18, and 24 weeks compared to baseline
   4. Proportion of subjects achieving HbA1c < 6.5% at 6, 12, 18, and 24 weeks compared to baseline
   5. Proportion of subjects achieving therapeutic response [change in HbA1c (baseline HbA1c – HbA1c at each evaluation time point) > 0.5% or HbA1c < 7%] at 12 and 24 weeks compared to baseline
   6. Change in blood pressure (systolic and diastolic) at 6, 12, 18, and 24 weeks compared to baseline
   7. Change in BMI and weight at 6, 12, 18, and 24 weeks compared to baseline
   8. Proportion of subjects with a reduction of 5% or more in weight and BMI at 6, 12, 18, and 24 weeks compared to baseline
2. **Exploratory Endpoints**
3. Change in lipid levels (total cholesterol, LDL-C, HDL-C, triglycerides) at 6, 12, 18, and 24 weeks compared to baseline
4. Change in liver function markers (AST, ALT, γ-GTP) at 6, 12, 18, and 24 weeks compared to baseline
5. Change in renal function markers (e-GFR, UACR, UGCR) at 6, 12, 18, and 24 weeks compared to baseline
6. Change in body composition analyzer indicators (skeletal muscle mass, body fat mass, body fat percentage, muscle mass, waist/hip circumference, body water, intracellular water, extracellular water, extracellular water ratio, abdominal fat percentage) at 12 and 24 weeks compared to baseline
7. Change in cardiovascular disease complication risk (ASCVD risk) at 12 and 24 weeks compared to baseline
8. **Safety Endpoints**
9. Laboratory tests, vital signs, physical examination results

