### Efficacy Analysis Set

Subjects who meet the inclusion/exclusion criteria, have been enrolled in this study, received the investigational product at least once, and have had their HbA1c level collected post-baseline will be included in the efficacy analysis set.

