### Safety Analysis Set

Subjects who meet the inclusion/exclusion criteria, have been enrolled in this study, received the investigational product at least once according to the approved indications, and have undergone safety evaluations will be included in the safety analysis set.

1. **Methods of Analysis**
2. **General Principles**

Continuous variables will be presented as descriptive statistics (number of subjects, mean, standard deviation, median, minimum, maximum), and categorical variables will be presented as frequencies and percentages. Unless otherwise specified, all tests will be two-sided with a significance level of 5%. All p-values will be reported to a maximum of three decimal places. If not exactly divisible, values will be rounded to two decimal places, rounding up at the third decimal place.

If missing data is minimal and evenly distributed, a complete-case analysis will be considered; multiple imputation methods will be employed if missing data is substantial or disproportionately distributed between groups. Sensitivity analyses will also be performed to ensure the robustness and validity of conclusions under various missing-data scenarios.

1. **Demographic and Baseline Characteristics**

For the demographic data (age, gender, etc.) and baseline characteristics of the study subjects, continuous variables will be presented as mean, standard deviation, median, minimum, and maximum values, while categorical variables will be presented as frequency and percentage.

To assess baseline comparability between intervention and control groups, standardized mean differences (SMDs) will be calculated for key baseline characteristics, including age, sex, HbA1c, BMI, and diabetes duration. Variables exhibiting significant imbalance between groups (SMD > 0.1) will be included as covariates in subsequent analyses.

1. **Efficacy Endpoints**

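### The primary HbA1c model uses only the week-24 change, although the efficacy set admits patients on any post-baseline HbA1c; a repeated-measures model would use the week-12 values already collected

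*Protocol*

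**What the plan says.** In Protocol section 7.2, Efficacy Analysis Set, enrolled and treated patients who "have had their HbA1c level collected post-baseline will be included in the efficacy analysis set" form the set. No time point is attached to that HbA1c. Under Primary Efficacy Endpoints the analysis is worded: "The change from baseline to 24 weeks will be analyzed using mixed-effects models or generalized estimating equations (GEE". The stated purpose of the model is to deal with clustering, and the structure given is imbalanced baseline covariates as fixed effects and "inter-center variability as random effects". No within-patient or repeated-measures term is mentioned.

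The General Principles of section 7.2 hold the missing-data rule, which has two branches. The first is worded: "If missing data is minimal and evenly distributed, a complete-case analysis will be considered". The second branch covers the remaining situations, where the protocol says that "multiple imputation methods will be employed if missing data is substantial or disproportionately distributed between groups". Further checks on the handling of missing values are planned as well. Neither minimal nor substantial is given a number, and the variables in the imputation model are not named.

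On data availability, the collection schedule says "Visit 2 (6 weeks) and Visit 4 (18 weeks) can be optional visits"; Visit 3 at week 12 carries no such label. Section 7.1 lists "Percent change and change in HbA1c at 6, 12, and 18 weeks compared to baseline" as a secondary endpoint. Sections 4.1 and 4.3 say that no visit or test is mandatory, and laboratory values are taken only where routine care produces them.

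**The concern.** A patient can enter the efficacy set on a week-12 HbA1c alone and then have nothing for the primary model to fit. What happens next depends on a switch with no threshold, applied once the missingness has been seen.

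Two things are at stake. One is precision: week-12 HbA1c is probably the best predictor of a missing week-24 value, and the complete-case branch does not use it. The other is protection against bias. The switch looks at how much is missing and whether it is balanced between groups. Loss that is equal in size in both arms, but related to week-12 control in only one of them, would pass the balance test and still distort the week-24 contrast. Imputing from baseline covariates alone would not correct that either.

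**Working it through.** **1. The plan's own figures (section 3.2).** Inputs: difference 0.4, SD 1.1, two-sided 5%, ICC 0.02, 20 patients per centre, 20% dropout; 24 institutions (synopsis). A two-sample t-test needs 240 in total at 80% power, 274 at 85% and 320 at 90%. The stated 274 therefore reproduces at 85%; the power is inferred, because the figure showing the calculation is not reproduced in the text. Design effect: 1 + (20 - 1) x 0.02 = 1.38. Then 274 x 1.38 = 378.1, and 378 / 0.8 = 472.5, so 473, against about 480 planned (24 x 20). With 20% lost, 480 x 0.8 = 384 remain, which exceeds 378.

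**2. Precision left unused by a week-24 complete-case analysis.** Let n_c be the number with a week-24 value, n_a the number with a week-12 or week-24 value, and r the correlation of the two changes. Let f be the share of patients without week 24 who have week 12. The documents give neither r nor f, so both are assumed over a range. The variance of the effect estimate is

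4 x SD^2 x [ICC/24 + (1 - ICC) x w],

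with w = 1/n_c using week 24 only, and w = (1 - r^2)/n_c + r^2/n_a using both visits. The effective number is 1/w.

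Week 24 only, 20% loss: 4 x 1.21 x (0.02/24 + 0.98/384) = 4.84 x 0.003385 = 0.01639, so SE = 0.128 and power = Phi(0.4/0.128 - 1.96) = 87.8%.

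Example with f = 1 and r = 0.7: w = 0.51/384 + 0.49/480 = 0.002349, giving an effective number of 425.7.

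| f | r | Effective number (384 without week 12) | Ratio 384/effective | Power gain, points |
|---|---|---|---|---|
| 0.25 | 0.5 | 389.7 | 0.985 | 0.35 |
| 0.5 | 0.5 | 395.0 | 0.972 | 0.7 |
| 0.5 | 0.7 | 406.1 | 0.946 | 1.3 |
| 1 | 0.5 | 404.2 | 0.950 | 1.2 |
| 1 | 0.7 | 425.7 | 0.902 | 2.3 |
| 1 | 0.8 | 440.4 | 0.872 | 3.0 |
| 1 | 0.9 | 458.2 | 0.838 | 3.75 |

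In the middle of this range the gain is about 1 to 3 points. It shrinks with the loss. For f = 1 and r = 0.7, 10% loss (432 completers) gives an effective number of 454.3 and a gain of 1.0 point. At 5% loss (456 completers) the figures are 467.5 and 0.5 point.

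**3. When bias arises.** A large-sample simulation took a true effect of -0.40, SD 1.1, r = 0.7 and the same percentage lost in each arm. Loss depended on week-12 HbA1c in one arm only, and the week-24 complete cases were analysed:

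| Loss per arm | Arm with dependence (log-odds per 1% HbA1c) | Week-24-only estimate |
|---|---|---|
| 20% | test (0.5) | -0.48 |
| 20% | test (1.0) | -0.54 to -0.55 |
| 20% | control (1.0) | -0.26 |
| 10% | test (1.0) | -0.48 |
| 10% | control (1.0) | -0.32 to -0.33 |
| 5% | test (1.0) | -0.44 |
| 5% | control (1.0) | -0.36 |

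Using week 12 as well returns -0.40 in every row. With the same dependence in both arms, the week-24-only estimate is also -0.40.

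**The case against.** A reader might infer that week-12-only patients contribute nothing to the primary result. The protocol does not say that. Its General Principles promise multiple imputation when missing data are substantial or uneven, and at 20% loss that is the natural reading. The 20% figures above describe a complete-case analysis that the plan would probably not run at that level. Where complete case does apply, loss is meant to be minimal, so the effect is smaller. This stands.

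A reader might also see a contradiction between the set and the model. There is none in the strict sense. One efficacy set serves all efficacy endpoints, a week-12-only patient belongs there for the week-12 secondary analyses, and leaving absent week-24 values to a missing-data rule is ordinary practice. This stands too.

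Availability of week-12 HbA1c should not be overstated. No test is mandatory, and patients lost before week 12 have no such value, so f may be low.

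Finally, the content of the imputation model is commonly left to the statistical analysis plan, and imputation that uses week 12 would target the same estimate as a repeated-measures model with similar efficiency. That is fair for the imputation branch. It does not answer the complete-case branch, which has no threshold and which tests only the amount and balance of loss. Nor does it change the fact that the protocol itself fixes the primary model as a single week-24 change with a centre effect, which is its natural reading.

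**Conclusion.** The point holds as a modest improvement to the primary analysis. As worded, the primary model gives a week-12-only patient no outcome. The complete-case branch drops such patients, and the imputation branch includes them without saying that their week-12 value is used.

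The precision cost is about 1 to 3 points of power at 20% loss under complete case, assuming r of 0.5 to 0.8 and at least half of the patients without week 24 having week 12. It is about 1 point or less at 10% loss with r up to 0.7. It would be wrong to conclude that the trial is underpowered for this reason: 384 completers cover the 378 required without any week-12-only patient.

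It would equally be wrong to say that the primary estimate is biased. The shifts shown need loss that depends on week-12 control differently by arm. The arms do differ in physician contact (section 4.4), so this is conceivable, but nothing in the document shows it. The bias figures illustrate what the missing-data switch could fail to detect.

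**What to change.** Reword Primary Efficacy Endpoints in section 7.2 so that the primary analysis is one linear mixed model of the HbA1c changes at weeks 12 and 24. It should have arm, visit and arm-by-visit as fixed effects alongside the covariates already planned, a clinic random effect and an unstructured within-patient covariance. Name the week-24 arm contrast as the primary estimate. The week-12 HbA1c secondary result can come from the same fit.

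The optional week-6 and week-18 values need not be included. A patient whose only post-baseline HbA1c falls at one of those visits would then still be in the set but outside the model, so report how many patients contribute at each visit.

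Keep multiple imputation, with week-12 HbA1c in the imputation model, and the other missing-data scenarios of the General Principles as sensitivity analyses. The primary estimate then no longer depends on an undefined choice between complete case and imputation.

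The cost is a change of wording; no new data are needed. The downsides are that a covariance structure must be specified (two visits need two variances and one covariance) and that the model relies on loss depending only on observed values. The retained sensitivity analyses should probe that assumption.

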**Protocol Synopsis**

| **Protocol Number** | DW_ODNENV_DB_01 |
| --- | --- |
| **Clinical Study Title** | A Primary Care-Based, Prospective, Multicenter, Cluster-Randomized, Pragmatic Clinical Trials to Determine the Effect of Linking data with Investigators When Using the Electronic Health Record-Linked Smartphone Application, ‘Well Check’, on Clinical Outcomes in Patients with Type 2 Diabetes Mellitus |
| **Protocol Version** | V1.1 |
| **Date** | 2024-05-16 |
| **Phase and Design** | Primary care-based, prospective, multicenter, cluster-randomized, pragmatic clinical study |
| **Clinical Study Sites** | 24 Primary Care Institutions Nationwide |
| **Objective of Clinical Study** | To confirm the improvement effects on clinical outcomes over 24 weeks in patients with Type 2 Diabetes using “Well Check” with or without investigator-linked management in real-world clinical settings |
| **Sponsor** | Daewoong Pharmaceutical Co., Ltd. |
| **Target Indication** | Type 2 Diabetes |

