## Rationale

Based on the pilot study results, the difference in average HbA1c between the test group and the control group after 24 weeks of using Well Check in Type 2 Diabetes patients was considered to be 0.4% (8.0% vs. 7.6%), with a standard deviation (*s*) of 1.1%. Referring to these results, the total sample size (*n*) required was estimated to be approximately 274 subjects using G*Power 3.1.9.7.

Since this study employs cluster randomization, we further adjusted the sample size calculation by incorporating the design effect to account for potential intra-cluster correlations among patients within the same clinic. We calculated the design effect using the standard formula:

$$Design effect=1+\left( m-1 \right)\times ICC$$

Referring to previous studies conducted in primary care settings for patients with type 2 diabetes [11, 12], we conservatively adopted an intraclass correlation coefficient (ICC) value of 0.02 and assumed an average cluster size (*m*) of 20 participants per center. Therefore, we calculated the resulting design effect to be 1.38, and applying this adjustment to the initial sample size estimate gives a revised total sample size of 378 participants. Finally, considering an anticipated dropout rate of approximately 20%, we adjusted the target recruitment number further to approximately 480 participants.

[figure not shown]

< Calculation for Subject Number – Based on Glycated hemoglobin>

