## Randomization

Due to the practical constraints of primary care settings, where it is challenging to manage test group and control groups separately within the same institution, cluster randomization will be used. Institutions will be randomized as either the test group [institutions managing subjects with the 'Well Check' app in conjunction with the investigator (responsible physician)] or the control group (institutions where subjects use the 'Well Check' app for self-management).

For cluster randomization, participating primary medical institutions will be divided into small groups based on basic characteristics [age of the treating physician (45 years and older, or younger), region (metropolitan, non-metropolitan)]. Within these small groups, the test group and control group will be randomly assigned in a 1:1 ratio using the cluster randomization method.

To ensure strict randomization, an independent person not related to this clinical study will prepare the randomization list using the Proc PLAN procedure of SAS (Ver. 9.4 or higher, SAS Institute, Cary, NC, USA). The generated randomization list will be provided to the IWRS (interactive web response system) developer. The randomization number will be verified through IWRS.

After obtaining written consent for participation in this clinical study, the subject's screening test results will be evaluated. Only those who meet the inclusion criteria and do not fall under the exclusion criteria will be assigned a Randomization Enrollment Number.

The randomization enrollment number will be given out as “AAA-RXX-YYY” and means the following.

- “AAA”: Institution identification number
- “R”: Cluster Randomization
- “XX”: Stratification identifiers [age of the treating physician (45 years and older, or younger), region (metropolitan, non-metropolitan)]

- “YYY”: Order of randomly assigned subjects

|  | Metropolitan (X1) | Non-metropolitan (X2) |
| --- | --- | --- |
| 45 years and older (1X) | 11 | 12 |
| 45 years or younger (2X) | 21 | 22 |

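### The primary analysis is left open between a mixed model and a GEE, with centre random effects given to both; with 24 clinics a GEE in its default form tests at about 7.4%, not 5%

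*Protocol*

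**What the plan says.** Protocol section 7.2, Primary Efficacy Endpoints: the change in HbA1c from baseline to week 24 is to be analysed with "mixed-effects models or generalized estimating equations (GEE"), so as to allow for clustering. The next sentence sets the model terms without separating the two options. "Patient-level covariates identified as significantly imbalanced at baseline (SMD > 0.1) will be included as fixed effects", and "inter-center variability as random effects".

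The paragraphs on secondary endpoints, exploratory endpoints, vital signs and laboratory tests repeat this pattern.

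The Synopsis gives the number of clusters as "24 Primary Care Institutions Nationwide". Section 4.5 has clinics "randomly assigned in a 1:1 ratio using the cluster randomization method", within strata of physician age and region. That makes about 12 clinics per arm. The general principles in section 7.2 state that "all tests will be two-sided with a significance level of 5" percent.

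The Synopsis row on statistical methods describes the same efficacy endpoints differently: two-sample t-tests or rank tests (Mann-Whitney, Wilcoxon), with no allowance for clustering.

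**The concern.** Three things are wrong with how the primary analysis is fixed.

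- Two analyses are permitted and there is no rule for choosing between them. The Synopsis adds a third, unclustered family.
- One option is mis-described. A GEE handles within-clinic dependence through a working correlation and a robust variance. It has no random effects, so the model terms as written cannot apply to it.
- The two options behave differently at this trial's size unless the inference is specified. The ordinary GEE robust variance is justified by a large number of clusters. With 12 per arm it is biased downward, and a normal reference ignores that it is itself estimated from few clinics. Both push the test above its nominal level.

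At stake is whether the two-sided 5% level holds for the primary comparison.

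**Working it through.** **Inputs from the protocol.** There are 24 clinics at 1:1, a two-sided level of 5%, and in section 3.2 a difference of 0.4, SD 1.1, ICC 0.02, 20 patients per clinic and 20% dropout. Evaluable patients per clinic: 20 × 0.8 = 16.

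**The plan's own figures.** A two-sided t-test with difference 0.4 and SD 1.1 needs 274 in total at 85% power. The power is inferred, since the visible text does not state it; 80% would give 240 and 90% would give 320. Design effect: 1 + 19 × 0.02 = 1.38. Then 274 × 1.38 = 378.1, and 378 / 0.8 = 472.5, close to 480 = 24 × 20. The chain reproduces, so 24 clinics of about 16 evaluable patients is the right setting for the check.

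**Closed form, equal clinic sizes, no covariates.** The estimated effect is the difference between two averages of 12 clinic means.

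- Let s² be the pooled between-clinic variance of those means, with 12 + 12 − 2 = 22 df. The unbiased variance of the effect is s² × 2/12.
- The uncorrected sandwich variance divides by 12 where the unbiased one divides by 11. It is therefore 11/12 of the unbiased variance.
- The GEE z-test rejects when |T| > 1.96 × √(11/12) = 1.877, with T distributed as t on 22 df under no effect.
- Size = 2 × P(t₂₂ > 1.877) = **7.4%**.

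This does not depend on the ICC or on the clinic size. It splits into two parts. An unbiased variance with a normal reference gives 2 × P(t₂₂ > 1.96) = 6.3%, and the 11/12 factor adds the rest.

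**Simulation under no effect (24 clinics, mean 16 per clinic).** The CV of clinic size is an assumption; the protocol gives none.

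| Test | Setting | Rejection rate |
|---|---|---|
| GEE, uncorrected sandwich, z; independence weights, 20,000 trials | ICC 0.02; CV 0 / 0.5 / 0.7 | 7.5% / 8.2% / 8.9% |
| Same | ICC 0.05; CV 0 / 0.5 / 0.7 | 7.4% / 7.8% / 9.3% |
| Same test, exchangeable weights, 3,000 trials | ICC 0.02; CV 0 / 0.5 | 7.4% / 8.3% |
| GEE, Mancl-DeRouen variance, t reference | eight settings, some with covariates and strata | 3.4–4.7% |
| Random-intercept model, REML, t on 22 df | equal sizes; ICC 0.02 / 0.05 | 4.3% / 4.9% |
| Same model, normal reference | equal sizes; ICC 0.02 / 0.05 | 5.5% / 6.2% |
| Unweighted clinic-mean t-test, 22 df | ICC 0.02; CV 0 / 0.5 / 0.7 | 5.0% / 4.9% / 4.9% |

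Simulation error is about ±1 percentage point at 3,000 trials. Further runs with exchangeable weights gave 7.2–7.7%, so 9% is the upper end of the range for unequal clinics.

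**The case against.** The strongest reply is that the protocol names a model class, not a test. It mentions no sandwich variance, no normal reference and no absence of a correction. Those details commonly belong in a statistical analysis plan, which is not at hand. This stands. A reader might infer that the trial's primary test will run at 7–9%, or that GEE is invalid here. The documents support neither: a corrected GEE with a t reference is equally permitted and held its level.

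A reader might also infer that the choice will be made after the results are seen. The protocol does not say when it will be made, and it could be fixed before database lock. Nor is the open choice costly once both options are corrected. Taking the smaller p-value of a REML model on 22 df and a corrected GEE on 22 df rejected 5.0% (equal sizes) and 4.7% (CV 0.5) at ICC 0.02, and 5.2% and 5.9% at ICC 0.05.

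A figure of 10–14% is also tempting. It appears when the uncorrected GEE carries both stratification factors, three covariates and unequal clinics. Section 7.2 does not put the stratification factors in the model, and the number of covariates is unknown in advance, so that range is not the protocol's.

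Finally, the random-effects phrase can be read charitably as meant for the mixed model alone, and a mixed model is not safe by itself. With a normal reference it gave 5.5–6.2%. Both points are fair, and both argue for stating the model and its degrees of freedom together.

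**Conclusion.** The point holds as a defect in the text of section 7.2. The primary analysis is not unique, the random-effects wording cannot apply to one of its two options, and the Synopsis names a third, unclustered approach. If the GEE option were run in its default form, its size would be 7.4% with equal clinics and no covariates. That result is exact for normally distributed clinic means. With clinic-size CVs of 0.5–0.7, which are assumed, the size would be about 7.5–9%. The inflation is conditional on the uncorrected variance and normal reference, which the protocol neither specifies nor excludes. It is not a property of GEE as such. The defect should be corrected before analysis; it does not touch recruitment, data collection or care.

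**What to change.** - **Primary endpoint.** Name one analysis: a linear mixed model with a random clinic intercept, fitted by REML, with Kenward-Roger or Satterthwaite degrees of freedom (about 20–22 for treatment).
- **GEE.** If kept, make it a sensitivity analysis with a named small-sample variance correction and a t reference. Tie the random-effects wording to the mixed model only.
- **Other endpoints in section 7.2.** Use the same mixed model for continuous outcomes. Four secondary endpoints in section 7.1 are proportions (HbA1c below 7%, HbA1c below 6.5%, therapeutic response, 5% weight or BMI reduction), and a linear model does not suit them. Specify a GEE with small-sample correction or a logistic mixed model for these.
- **Synopsis.** Replace the unclustered t-test and rank tests with the model chosen in section 7.2.

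The cost is wording, plus an interval wider by 2.07 / 1.96 = 1.06, about 6%. In power terms, take 24 × 16 = 384 evaluable patients and a design effect of 1 + 15 × 0.02 = 1.30. The standard error is 1.1 × √(4 × 1.30 / 384) = 0.128, and 0.4 / 0.128 = 3.12. Power is then about 85% on 22 df, against 88% with a normal reference. That is still close to the 85% inferred from the plan's sample size.

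### The primary model leaves out the two factors used to stratify the clinic randomisation; to the extent they are prognostic, precision is lost, and adding them needs small-sample inference

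*Protocol*

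**What the plan says.** Protocol section 4.5 (Randomization) forms groups of clinics "based on basic characteristics [age of the treating physician (45 years and older, or younger), region (metropolitan, non-metropolitan", which gives four strata. It then states: "Within these small groups, the test group and control group will be randomly assigned in a 1:1 ratio using the cluster randomization method". The Synopsis gives the number of clusters as "24 Primary Care Institutions Nationwide".

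Section 7.2 (Primary Efficacy Endpoints) calls for a mixed-effects model or GEE and sets a rule for its terms: patient-level covariates whose baseline standardised mean difference exceeds 0.1 "will be included as fixed effects, and inter-center variability as random effects". The variables to be screened for imbalance are described earlier in section 7.2 as "key baseline characteristics, including age, sex, HbA1c, BMI, and diabetes duration". The secondary, exploratory and safety paragraphs repeat the pattern of patient-level covariates plus a centre effect. The Synopsis lists simple two-sample tests, also without strata. Physician age, region or stratum appears in no model.

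In the strata table of section 4.5 the second age row is labelled "45 years or younger (2X)", whereas the text of the same section sets the cut at 45 and older versus younger.

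**The concern.** Stratified randomisation balances the arms on the stratification factors, so differences between strata largely drop out of the treatment contrast. If the model does not contain those factors, the same differences stay in the centre random effect and are counted as noise. The estimate remains unbiased, but its standard error is larger than the design warrants.

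The rule in section 7.2 works against these two factors in two ways. It admits patient-level covariates only, and physician age and region belong to the clinic. It also admits only variables found imbalanced, and stratification exists to prevent imbalance on these two. They are therefore left out by a stated rule rather than by silence. With 24 clinics, precision depends heavily on between-clinic variance.

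**Working it through.** **Inputs.** From section 3.2 (Rationale): difference 0.4, SD 1.1, ICC 0.02, 20 patients per centre, 274 patients before inflation, design effect 1.38, 378 after inflation, 20% dropout, about 480 recruited. From section 7.2: two-sided 5% level. From the Synopsis: 24 clinics. Assumed, because the protocol does not give them: the share *f* of between-clinic variance explained by the strata, and equal strata of six clinics split 3:3 with equal clinic sizes.

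**Reproducing the plan's figure.** The readable text states no power. A two-sample t-test with difference 0.4 and SD 1.1 needs 240, 274 and 320 patients in total for 80%, 85% and 90% power, so 85% is the value that fits. Design effect: 1 + 19 × 0.02 = 1.38. Then 274 × 1.38 = 378.1, and 378 / 0.8 = 473, close to 480 = 24 × 20.

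**Standard error.** The between-clinic variance is 0.02 × 1.1² = 0.0242 and the within-clinic variance is 1.21 − 0.0242 = 1.1858. With 378 completers,

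SE² = 4 × [0.0242 × (1 − f) / 24 + 1.1858 / 378].

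- Strata left in the error (f = 0 in the formula): 4 × (0.001008 + 0.003137) = 0.01658, SE 0.1288.
- f = 0.25: 4 × (0.000756 + 0.003137) = 0.01557, SE 0.1248, ratio 1.032.
- f = 0.60: 4 × (0.000403 + 0.003137) = 0.01416, SE 0.1190, ratio 1.082.

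The excess that the unadjusted model actually reports is slightly larger, because the stratum sum of squares for 24 clinics is spread over 22 degrees of freedom. With 378 / 24 = 15.75 completers per clinic, the residual variance of a clinic mean at f = 0.60 is 0.00968 + 0.07529 + (24/22) × 0.01452 = 0.10081 without strata and 0.08497 with them. The ratio of standard errors is √1.1864 = 1.089. The same step at f = 0.25 gives 1.035. Hence about 3–9%.

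**Power and type I error.** Simulated clinic means, ICC 0.02, t reference on 22 df without strata. With strata, the reference has 19 df (four-level stratum), or 20 df (two main effects) in the rows marked *.

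| Share f | Type I without strata | Power without | Power with | Gain (points) |
|---|---|---|---|---|
| 0 | 5.1% | 84.5% | 83.9% | −0.6 |
| 0.10 | 4.8% | 84.6% | 84.7% | 0.1 |
| 0.25 | 4.3% | 84.8% | 86.0% | 1.2 |
| 0.30* | 4.1% | 85.2% | 86.9% | 1.7 |
| 0.50 | 3.7% | 85.4% | 88.1% | 2.7 |
| 0.60* | 3.5% | 85.7% | 89.1% | 3.4 |
| 1 (bound) | 2.5% | 86.9% | 92.3% | 5.4 |

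With strata, type I error stays at about 5%. At f = 0 the cost with two main effects is about 0.3 points rather than 0.6.

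**Sensitivity to the ICC.** At an ICC of 0.05, which the protocol does not assume, power goes from 73.5% to 77.1% at f = 0.25 and from 74.4% to 82.4% at f = 0.50.

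**GEE without correction.** Section 7.2 also allows GEE. With an uncorrected robust variance and a normal reference, at ICC 0.02 and f = 0, 0.3 and 0.6, type I error is 7.1%, 6.3% and 5.4% without the factors and 8.6%, 8.9% and 9.0% with them.

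**The case against.** Four points can be made on the other side.

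- **The list of model terms may not be closed.** Section 7.2 says what will be included, the list of screened variables is open-ended, and a full specification often sits in the SAP, which is not shown. This has some force. But section 7.2 does state an entry rule, and clinic-level factors balanced by design do not meet it.
- **The loss is conditional.** A reader might infer that the standard error is certainly too large and power certainly given away. The protocol says nothing on how strongly physician age or region relates to HbA1c change. If they are unrelated, adjustment loses a little power. Patient covariates that enter under the 0.1 rule could also absorb part of any stratum difference. This stands, and limits the claim.
- **The test need not be conservative.** A reader might infer that omitting the strata always makes the planned test conservative. That holds for a calibrated small-sample test. An uncorrected GEE test is not conservative either way, and adding the factors takes it further from 5%. This stands, and it changes the fix.
- **The age label is minor.** A reader might infer that a clinic with a 45-year-old physician has two valid stratum codes. The text of section 4.5 places age 45 in the older group; only the table label is loose. This stands too.

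**Conclusion.** The point holds in conditional form. The model fixed in section 7.2 does not match the stratified design in section 4.5. To the extent the strata are prognostic, and with a calibrated small-sample test, the standard error is overstated and the test conservative. At the planned ICC of 0.02 and 378 completers, a share of 25–60% means a standard error about 3–9% too large and about 1–3.5 points of power lost. A share of zero means adjustment costs about 0.3–0.6 points, and break-even is near 10%. The share, the equal strata and the equal clinic sizes are assumptions.

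The documents do not support a larger claim. With a calibrated test the omission neither biases the estimate nor inflates type I error, and the bigger power differences need an ICC above the protocol's own. It is a worthwhile, nearly free improvement rather than a threat to validity. The age-45 label is a wording correction and adds no weight to the statistical point.

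**What to change.** In section 7.2, state that physician-age stratum and region enter the between-arm models as fixed effects regardless of observed imbalance. In the same place, specify small-sample inference for 24 clinics: for example Kenward-Roger or Satterthwaite degrees of freedom for the mixed model, or a bias-corrected sandwich variance with a t reference for GEE. The two parts belong together, because the factors without the correction would leave a GEE test at about 9% type I error.

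In the strata table of section 4.5, change the second age label to 'younger than 45 years' so that it agrees with the text.

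Cost: 2 of 22 degrees of freedom, a short addition to section 7.2 and one table label. No new data are needed, since the stratum code is already part of the randomisation number.
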